#### Myotonometry

MyotonPRO (MyotonAS, Tallinn, Estonia) will be used to measure muscle tone, stiffness, and elasticity of the quadriceps femoris muscle [47]. The device will be positioned at 2/3 between the ASIS and the upper pole of the patella [48], at the midpoint between them and 2 cm to the medial and 2 cm to the side, 15 cm from the AIIS and 4 cm from the base of the patella.

The device will be positioned perpendicular to the evaluated region, with light pressure. This preload is controlled and corresponds to 0.18 N of initial compression of the subcutaneous tissue, after which an additional impulse of 0.40 N will be released, with a duration of 15 ms. This impulse will induce oscillation in the tissue, which will be damped or deteriorated [49].

#### Electrical bioimpedance (BIA)

Electrical bioimpedance will be assessed using tetrapolar electrodes (BIA Analyzer, Nutritional Solutions Corporation, Harrisville, MI, USA, *f* = 50 kHz, and 800 μA) [50, 51]. Global and localized evaluations will be carried out. The global assessment will take place with the participant in the supine position; the electrodes will be positioned on the dominant hand (base of the 3rd metacarpal phalanx and between the styloid process of the radius and the head of the ulna) and on the dominant foot (at the base of the 3rd metacarpal phalanx and in the anterior region of the ankle, between the malleoli). The localized evaluation will be carried out to evaluate the quadriceps femoris muscles; the electrodes will be positioned five centimeters below the EIAS and above the base of the patella. The BIA components analyzed will be resistance R, reactance (Xc), and phase angle (phA) [51, 52]. The analysis of the tolerance ellipse will also be performed. The Bioscan program: BL-960141 (Biologica, Barcelona, ​Spain) will be used for the analyses [50, 51].

#### Maximal voluntary isometric contraction (MVIC)

For MVIC evaluation, the participant will be positioned with the dominant lower limb on the Biodex System Pro isokinetic dynamometer (Biodex Medical System, Shirley – NY, USA). According to the protocol suggested by Baroni et al. [53], prior to the evaluation, the volunteer will be submitted to a warm-up, which will consist of ten repetitions of concentric contractions of knee flexion-extension at 180°/s throughout the range of motion.

Muscle function will be assessed by means of the highest torque value obtained between three repetitions of 5 s of maximum voluntary contraction at 60° of knee flexion (with 0° corresponding to the maximum extension). A two-minute interval between repetitions will be administered in order to minimize the possible effects of fatigue. The participant will be instructed to give their maximum strength and will be verbally encouraged by the researcher in each maximum voluntary contraction.

#### Sample calculation

The sample calculation was performed based on the study by Bailey et al. [54], using the CK variable, since this variable expresses the amount of muscle protein in the blood representative of indirect muscle damage. The G*Power 3.1.9.7 software was used. Considering the standard deviation in the CK concentration of 200 μL, using a two-tailed hypothesis test with 80% test power and 5% significance level, a sample size of 16 participants per group was stipulated. Predicting sample loss, 4 participants per group were added totaling 80 participants. To increase the participants’ adherence to the intervention, telephone contact will be made daily to encourage them to remain in the study, and thus avoid losses. In case of discontinuity or withdrawal, the intention to treat will be used.

### Statistical analysis

The normality of the data will be verified by the Kolmogorov Smirnov test. If normality is detected, the sample characterization variables will be presented as mean and standard deviation, if not, as median and interquartile range. To compare the characterization of the sample, one-way ANOVA with Tukey’s post test or Kruskal-Wallis with Dunn’s post test will be used depending on the normality of the data.

The comparisons of the outcomes between the four groups studied and the moments will be performed using the technique of analysis of variance for repeated measures model in the two-factor scheme, which will provide information on the effects of time, group, and interaction. The repeated measurement data will be checked for sphericity violation using Mauchly’s test and the Greenhouse-Geisser correction will be used when the sphericity is violated. For moment analysis, Bonferroni’s post-test for parametric distribution or Dunn’s post test for non-parametric distribution will be used and the analysis between the groups will be performed using one-way ANOVA or the Kruskal-Wallis test.

In addition, the effects of the groups studied will be verified for all the outcomes assessed by calculating the effect size (ES) using Cohen’s *d*, considered as “null” (< 0.2), “small” (≥ 0.2), “moderate” (≥ 0.6), “large” (≥ 1.2), or “very large” (≥ 2.0) [55].

An intention-to-treat analysis will be performed using the patient’s most recent assessment in case of withdrawals or absence of data. The level of significance will be p < 0.05 for all tests. The statistical program SPSS (version 24.0) (SPSS Inc., Chicago, IL, USA) will be used for the analyses.

The external evaluator will enter the data into the database for screening, randomization, and statistical analysis purposes. Double data entry in electronic format will be used. Data integrity will be monitored by regularly scrutinizing data files for omissions and errors. Participants will be given an anonymous study ID to protect confidentiality, and only study investigators will have access to the final trial data set. The spreadsheets containing the raw numeric data of the data generated in this study will be stored in its entirety initially on two external hard drives and two online clouds. Any data required to support the protocol can be supplied on request.

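### The intention-to-treat rule is last observation carried forward; on outcomes that worsen and recover over 96 h it can bias the group contrasts and the interaction when data are missing and loss or true curves differ between arms

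*Protocol article*

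**What the plan says.** The rule stands in the Statistical analysis section: the intention-to-treat analysis is to use the participant's "most recent assessment in case of withdrawals or absence of data". It covers single missed visits as well as withdrawals. The Sample calculation section repeats the label without a method ("In case of discontinuity or withdrawal, the intention to treat will be used") and allows for loss: "Predicting sample loss, 4 participants per group were added totaling 80 participants".

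The planned analysis of outcomes is an "analysis of variance for repeated measures model in the two-factor scheme, which will provide information on the effects of time, group, and interaction", so carried values enter it as if they had been measured. The article names no other way of handling missing data, and its Strengths and weaknesses section counts the intention-to-treat approach as a mark of quality.

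Outcomes are taken before exercise, immediately after it, and at 24, 48, 72 and 96 h. Two departures matter here. The section on primary and secondary outcomes omits ultrasound immediately after exercise. Perceived recovery is first rated immediately after exercise and has no baseline.

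**The concern.** Carrying a value forward is harmless only if the outcome would have stayed flat after the last visit. The trial's stated aim is to study acute and delayed responses during recovery, so the outcomes are expected to move.

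The schedule sharpens the problem. Muscle thickness is a primary outcome. A participant lost before 24 h has no post-exercise thickness, so a pre-exercise value is carried to 96 h. (The Study design section reads as if every outcome were repeated right after exercise; the example follows the explicit ultrasound exception in the outcomes section.) For perceived recovery, the same participant carries the rating given straight after exercise to 96 h.

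Loss need not be equal or unrelated to outcome. The Participants section removes people for health problems, for using medication or other therapy, or because they wish to leave, and these can follow from pain. The arms differ in cuff pressure, and the article says that participants are not blind. At stake are the between-group comparisons at 24–96 h and the interaction, which carry the trial's conclusion.

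**Working it through.** **Inputs from the protocol.** 20 per group, 1:1:1:1 allocation; visits immediately after exercise and at 24, 48, 72 and 96 h; two-sided 5% level; SD of CK 200 (unit printed as μL). Loss allowance: 4/20 = 20%. The plan's own figure reproduces: 16/(1 − 0.20) = 20 per group, and 4 × 20 = 80.

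**Inputs not in the protocol, assumed here.** It gives no expected means by visit and no loss by arm. Two illustrations are used:
- MVIC, % of baseline: 70 immediately after, then 75, 82, 88, 94 at 24–96 h; SD 10–15; within-person correlation 0.6.
- CK, immediately after and at 24–96 h: control 200/450/600/700/650, IPC 200/350/450/500/450; SD 200; correlation 0.7.

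Loss is unrelated to outcome in both. Error and power come from simulating a two-arm t test at 96 h.

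**Formula.** Bias of an arm's mean = fraction lost × (mean at last visit − true mean at the later visit). Bias of a contrast = the difference between the two arms' biases.

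**MVIC, no true effect, 4 of 20 lost in one arm and none in the other.**

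| Last visit | Bias of the 96 h mean | Type I error, carry-forward |
|---|---|---|
| Immediately after | 0.2 × (70 − 94) = −4.8 | 12–18% |
| 48 h | 0.2 × (82 − 94) = −2.4 | 7–9% |
| 72 h | 0.2 × (88 − 94) = −1.2 | about 6% |

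Analysing observed values only keeps the error at about 5%. With 2 against 0 lost right after exercise it is about 6–7% under carry-forward; with 1 against 0, about 5%.

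**MVIC, loss in both arms right after exercise.** With no true effect, 4 against 2 gives 3–4% and 4 against 4 gives 1–2%. The test is conservative because mixing 4 early values with 16 late ones widens the spread. The added sample variance is (4 × 16/20) × 24²/19 = 97. At SD 10 the ratio to the true variance is (100 + 97)/100 = 1.97; at SD 15 it is (225 + 97)/225 = 1.43.

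Now suppose a true difference that grows from 0 right after exercise to 10 points at 96 h, SD 10, 4 against 4 lost. The expected estimate is 0.8 × 10 + 0.2 × 0 = 8. Power is about 27%, against 78% on observed values.

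**CK, all loss before 24 h, contrast control minus IPC at 96 h.**
- No true effect, 20% against 5% lost: 0.20 × (200 − 650) − 0.05 × (200 − 650) = −67.5; type I error 12.7%.
- No true effect, 20% against 20%: −90 + 90 = 0.
- True difference 200, 20% against 20%: 0.20 × (200 − 650) − 0.20 × (200 − 450) = −40; power 51%, against about 78% on observed values.
- True difference 200, 20% control against 5% IPC: −90 + 12.5 = −77.5.
- True difference 200, 5% control against 20% IPC: −22.5 + 50 = +27.5.

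The last two lines show the sign reversing with the arm that loses more. If loss is spread over the visits the effects are smaller: type I error 6.6% in the first case and power 72% in the third.

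**The case against.** A reader might infer that the rule biases every comparison from 24 to 96 h. It does not. With no missing data nothing is carried forward. With no true effect, and loss that is identical in amount and timing and unrelated to outcome, the between-group bias is zero, although each arm's own curve is still wrong.

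A reader might also infer that treating filled values as observed understates the variance. The MVIC example shows the opposite: the 96 h variance in the affected arm is 1.4–2.0 times the true one. All that can be said in general is that the variance is misstated.

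The 12–18% error is a selected corner. The allowance of 4 applies to every group and is not a forecast of one-sided loss. Participants are healthy volunteers, follow-up lasts five consecutive days, and daily telephone contact is planned, so actual loss may be small. Further sensitivity analyses may also sit in an analysis plan that is not shown, so their absence from the article is no fault.

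All of this stands, and it limits the size of the problem. It does not rescue the rule. The article commits to carry-forward as the primary handling, the sample size plans for 20% loss, and equal loss still shrinks a real effect and costs power.

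**Conclusion.** The concern holds as a conditional one. The rule is last observation carried forward under an intention-to-treat label, applied to outcomes that rise or fall and then recover. When data are missing and either the loss or the true curves differ between arms, the 24–96 h contrasts and the interaction can be biased towards or away from an effect.

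On the assumed courses, the harm ranges from nothing, through a type I error of about 5–9% for one-sided late loss (last visit at 48–72 h), to 12–18% for one-sided early loss. Under balanced early loss the main harm is to power: about 27% against 78% for MVIC and 51% against about 78% for CK. These sizes rest on assumed means, SDs (for MVIC), correlations and loss patterns, which the protocol does not give. That the method is ill-suited to the outcomes follows from the design itself.

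**What to change.** In the Statistical analysis section, replace the carry-forward sentence. Analyse all randomised participants with a likelihood-based linear mixed model on every observed visit, with group, moment and group × moment, and baseline as a covariate where one is measured (perceived recovery has none). This is valid under missing at random and is available in the planned software (SPSS MIXED).

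Prespecify the covariance by outcome:
- Unstructured for outcomes with few moments.
- A simpler structure for lactate. It has 3 + 8 + 4 = 15 moments, and an unstructured matrix would need 15 × 16/2 = 120 parameters from 80 people (14 × 15/2 = 105 with baseline as a covariate).

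Transform skewed outcomes such as CK if needed. Keep carry-forward at most as a labelled sensitivity analysis, and add one that allows for outcome-related loss. State how participants removed under the Participants section fit with the intention-to-treat set.

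The cost is changed wording and modest extra modelling, with no new data. Settle it before any unblinded analysis.

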## Discussion

### Potential impact and significance of the study

This IPC protocol follows the application time pattern found in the literature, however, with different occlusion pressures. Thus, the study findings could bring a new strategy to reduce muscle damage caused by exercise, based on the dose response. Thus, if the hypothesis of the present study is proven, physically active people could benefit from the technique, since it is easily accessible and applicable, in addition to being low cost.

It is also worth noting that the study aims to analyze the participants’ perceptions of the different IPC protocols, especially pain and recovery. Thus, these results may add elements that favor the use of IPC protocols and guarantee the adherence of this pre-exercise strategy.

### Strengths and weaknesses of the study

A strong point of the study is the comparison between two different IPC protocols with a placebo group and a control group, thus making it possible to observe the true results found from each intervention. The fact that the technique uses only a pressure cuff makes it easy to apply and access, so that it can be implemented in prevention and rehabilitation centers. Another positive point of the study is the monitoring of the effects of the technique for up to 96 h after the intervention, in addition to the high methodological quality of the study characterized by prospective registration, randomization, blinding, and intention to treat approach. However, a limitation of the study is the fact that the therapist and participants are not blind. Finally, some participants may be injured due to the strenuous protocol of eccentric exercise performed.

### Contribution and clinical applicability

As already described, the technique is easy to apply, low cost, and non-invasive. It can be applied in different environments of prevention, rehabilitation, and functional recovery. The data obtained in the present study could be used for better application of the technique in physiotherapy, especially in sports clinical practice, considering the periods of training and, especially, competition, providing protection from EIMD.

It is also worth noting that this study includes the items on the checklist for protocol studies in order to minimize bias, and was prospectively recorded. The outcomes will be disseminated through publications in scientific journals and presentations at congresses in the area.

### Trial status

Number Protocol: NCT04420819

Patient recruitment is currently underway.

Study start date: April 2021

Primary completion date: June 2021

Study completion date: December 2021

Finished recruitment: November 2021

## Data Availability

The spreadsheets containing the raw numeric data will be stored on two external hard drives and two “clouds.” After analyzing the data, scientific articles related to the study will be made, and after publication, the data will remain preserved and will also be shared and made available in its entirety for a period of 5 years. The datasets analyzed during the current study are available from the corresponding author on reasonable request.

## Abbreviations

BIA: Electrical bioimpedance
CEAFIR: Center for Studies and Assistance in Physiotherapy and Rehabilitation
CK: Creatine kinase
MVIC: Maximal voluntary isometric contraction
EIMD: Exercise-induced muscle damage
EE: Eccentric exercise
ASIS: Antero-superior iliac spine
AIIS: Antero-inferior iliac spine
VAS: Visual analog scale
IPC: Ischemic preconditioning
TOP: Total occlusion pressure
RF: Femoral rectum
VL: Vastus lateral
